### Data collection and assessments

At enrolment, participants will give their informed consent through consent forms. Subsequently, participants will be provided with two online quantitative questionnaires to fill out, utilizing baseline data for the study (T0). Upon completion of P4HP, participants are provided the same two online quantitative questionnaires (minus sociodemographic data) to respond to the post-intervention assessment (T1) (Fig. 3). The first questionnaire assesses diet quality [73]. The term diet quality has been used in recent decades to evaluate the dietary habits or patterns of a population and the efficacy of dietary interventions [74–76]. Diet quality is a suitable term to present multiple food components, assessed using an index to evaluate the extent of adherence to dietary guidelines. The second questionnaire includes all other assessments and is distributed using Qualtrics. Access to all data collection tools and databases is strictly limited and regulated through personal user profiles. Both platforms are password-protected and all data will be regularly backed up into a password-protected database.

**Fig. 3 Fig3:**
[figure not shown]
P4HP C-CRT SPIRIT diagram

#### Sociodemographic data

Questions to collect name, year of birth, phone number, email, postal code digits, living situation, ethnicity, educational level, and personal and household income.

#### BMI

Two questions to collect height and body weight.

#### Diet quality

We derive scores for diet quality using Eetscore [77]. Eetscore is a validated web-based screening tool to determine the diet quality of Dutch adults and suitable for assessing change in diet quality over time. Eetscore consists of a short food frequency questionnaire in an accessible writing style that is scored with the Dutch Healthy Diet index 2015 (DHD2015-index) to assess adherence to the Dutch food based dietary guidelines of 2015 of the Dutch health Council [73]. The DHD2015-index has been validated with 24 h dietary recall and FFQ data. In addition, to the DHD2015-index, a 16th component for unhealthy choices has been added. The questionnaire to determine this diet quality score consists of 40 questions with sub-questions inquiring about the consumption of 54 foods or food groups. Based on the answers a total score and 16 sub scores will be calculated. Sub scores of Eetscore are available for 1) vegetables, 2) fruit, 3) whole grain products, 4) legumes, 5) nuts, 6) dairy, 7) fish, 8) tea, 9) fats and oils, 10) coffee, 11) red meat, 12) processed meat, 13) sugar-containing beverages, 14) alcohol, 15) sodium and 16) unhealthy choices. Each component will be scored on a scale ranging from 0 (non-adherence) to 10 (complete adherence), providing a total score between 0 and 160. For the calculation of the scores, specific cut-off and threshold values are used. Since Eetscore is developed for the general Dutch adult population, it has been adapted to fit the requirements of pregnant women. The (sub)scores were adapted based on the dietary recommendations for pregnant women provided by the Dutch Health Council and the Netherlands Nutrition Centre [78]. We use the web-based version of Eetscore which can be filled out in about 10-15 min.

#### Empowerment

Empowerment will be assessed using the Pregnancy-Related Empowerment Scale (PRES). This is a valid and reliable assessment containing 16 questions on women’s health-related empowerment during pregnancy [79].

#### SOC

We derive SOC scores from the three-item SOC questionnaire (SOC-3) [80, 81]. This validated questionnaire includes three questions; all corresponding to the three components of SOC: comprehensibility (“Do you usually feel that the things that happen to you in your daily life are hard to understand?”), manageability (“Do you usually see solutions to problems and difficulties that other people find hopeless?”), and meaningfulness (“Do you usually feel that your daily life is a source of personal satisfaction?”) [80–83]. Participants can indicate their answer as 1 (yes, usually), 2 (yes, sometimes), or 3 (no). The sum of these three items (after reverse coding of the comprehensibility item) reflects the total SOC, with higher scores indicating a weaker SOC. Participants are divided into three SOC groups: weak (scores 6–9), intermediate (scores 4–5), and strong (score 3) - in line with previous studies [80, 84, 85]. We use a Dutch version of the SOC-3, a short version of the original to alternatively measure change, as previously used by Herens [85–87]. SOC can be influenced by interventions and has been previously linked to the concept of empowerment [56, 57].

#### QoL

We derive a score for global QoL using a Visual Analogue Scale (VAS): a horizontal line of 100 mm, with stops (“anchors”) at both extremes – 0 (worst imaginable QoL) to 100 (perfect QoL) – representing the limits of self-rated QoL. A QoL VAS is a frequently used single-item technique with good to excellent levels of reliability, validity, and sensitivity [88–90].

#### SRH

We derive a score for SRH using a General Self-Rated Health (GSRH) question. Asking people to rate their health in surveys provides an easily assessed, common indicator of health [91–95]. Respondents are asked to rate their health, in general, as ‘excellent’, ‘very good’, ‘good’, ‘fair’ or ‘poor’.

### Process evaluation

To perform a process evaluation, P4HP will be evaluated in terms of multidisciplinary collaboration, facilitators, and barriers by in-depth interviews with a purposeful sample of midwives, dieticians and pregnant women involved in the C-RCT. Semi-structured interview guides will be prepared for each of the interviews with midwives, dieticians, and pregnant women. 10-15 interviews will be performed with each of the three groups, depending on data saturation, and performed at T1.

### Intervention

P4HP is a non-invasive empowerment intervention and consists of four extra moments for pregnant women to discuss nutrition with their midwife and a dietician. P4HP distinguishes itself from standard birth care by its empowering approach towards improving diet quality during pregnancy. The intervention is free of charge for the women and takes place in an individual or group setting (via CenteringPregnancy). P4HP is designed to be flexible, meaning that the professional has the freedom to adapt to what the individual or group needs at each session. This research is in line with current Dutch policy regarding empowerment, dietary guidelines, and prevention [96–99].

Table 1 provides an overview of the P4HP-elements. For each element of the intervention, it explains the goal(s), the activity, the estimated time that is needed for the activity, and the tools as well as who guides the activity. The exact time investment per session topic will be discussed with and adapted to the possibilities of the midwives and dieticians.

**Table 1 Tab1:** Overview of the P4HP-intervention

Session	Time	Goal(s)	Activities	Tool
**1. Early nutritional information with midwife (4-10 weeks of participants’ pregnancy)**				
**A) Individual setting**	15 min	Gain insight into perspectives of the women towards nutrition and create a sense of urgency for healthy nutrition during pregnancy Identify aspects that go well regarding nutrition and define at least one achievable step the woman is willing to work on Create a positive attitude towards nutritional changes Understand the complexity of each woman’s situation regarding healthy nutrition	First interview on nutrition	Visual aid to guide the interview and write down action points Motivational Interviewing
**2. Appointment with dietitian (~ 12 weeks of participants’ pregnancy)**				
**A) Individual setting**	30-45 min	Support women in developing strategies to cope with individual challenges Provide more in-depth information	Discuss challenges in healthy nutrition based on the woman’s individual needs	Visual aid to guide the interview and write down action points
**B) Group setting**	60 min	Support women in developing strategies to cope with individual challenges Provide more in-depth information Peer support and learn from each other’s questions and experiences	Workshop with group discussions on challenges in healthy nutrition based on the women’s individual needs Use each other’s experiences to find individual coping mechanisms	Visual aid to guide the interview and write down action points
**3. Reflection moments with midwife (~ 22 and ~ 32 weeks of participants’ pregnancy)**				
**A) Individual setting**	15 min	Increase awareness of the connection between the women’s actions and results on diet quality Increase abilities to identify actionable and achievable goals that lead to improved diet quality	Facilitate women’s reflection on their nutrition and the efforts they made in the last weeks Identify next steps for improvement, if achievable at that moment	
**B) Group setting**	30 min	Increase awareness of the connection between the women’s actions and results on healthy nutrition Increase abilities to identify actionable and achievable goals that lead to improved diet quality Peer support and learn from each other’s questions and experiences	Facilitate women’s reflection on their nutrition and the efforts they made in the last weeks Identify next steps for improvement, if achievable at that moment	

The financial compensation for the invested time by midwives and dieticians will be reimbursed. Participating women will not have additional costs as compared to standard birth care.

### Control

Midwifery practices in control clusters will provide participating women with standard birth care (according to the present Dutch birth care standards [100]) and the usual information on nutrition during pregnancy. There is no standard protocol for nutrition communication in antenatal care, so the amount of time and content can vary between the control practices. It is common practice to dedicate a small amount of time (2-10 min) to the discussion of nutrition at the first consultation, focusing on foods that cannot be safely consumed during pregnancy. In standard birth care, pregnant women may be referred to organizations such as the Netherlands Nutrition Centre for questions, nutritional guidelines, or advice. Frequently used tools such as the app ZwangerHap [101] are likely used by pregnant women in the control group. In addition, the newest dietary guidelines for pregnant women of the Dutch Health Council are freely available for health professionals and pregnant women. Being part of the control group in no way limits the use of such nutritional resources, as they are part of standard birth care. Outcome measures will be obtained in the same way for participants in the control clusters as for those in intervention clusters at baseline (T0) and follow-up (T1).

### Ethical consideration

Ethics approval was given by Medical Research Ethics Committee Utrecht, the Netherlands on September 21st 2021. The committee thereby declares that the proposal satisfactorily deals with ethical issues and that it complies with the Netherlands Code of Conduct for Scientific Practice. Because of negligible risk for participants, the MREC Utrecht has granted this study exemption from the obligation to the insurance that covers damage caused by the research through injury of the participant. Therefore, adverse events are currently not foreseen, due to the nature of the study and intervention. Informed consent will be obtained from each participant, after the purpose and possible consequences of the study have been explained. This study will be conducted according to the principles of the Declaration of Helsinki (October 2013) and according to the Medical Research Involving Human Subjects Act (WMO).

Participation in the study is voluntary and participants can leave the study at any time for any reason if they wish to do so without any consequences. They are asked to inform either the principal investigator or intervention deliverer (midwife or dietician) about their decision. Participants are not obliged to inform the researchers about their reason to withdraw. The investigator can decide to withdraw a participant from the study for urgent medical reasons, such as having a miscarriage or a pregnancy with extreme complications. The reason for withdrawal reason will be kept for the record for further study. Since P4HP is possibly delivered in a group format, there will be no replacement of individual participants after withdrawal.

### Data analyses

#### Quantitative analyses C-RCT

Statistical analyses will be carried out using IBM SPSS Version 25 (Statistical Package for Social Sciences). Data cleaning will be performed before the final review to check for missing data or outliers. We expect data missing will be at random, and if so, all available data from T0 and T1 will be used to conduct the analyses.

All data will be quantitatively presented in tables (Tables 2 and 3). BMI, the DHD2015-index, PRES score, SoC-3 score, QoL VAS score, and GSRH-score will be presented as ordinal data. Ethnicity, education, and living situation will be presented as nominal data. All data will be entered and verified, and scores will be calculated for multiple-item instruments (i.e. DHD2015-index, PRES, SoC-3). Descriptive statistics will be performed to tabulate mean (or median) values of all study characteristics and baseline values of the independent variables. Chi-square (for categorical variables) and Student’s t-tests (for continuous variables) will be used to compare the descriptive statistics between study groups and to identify potential covariates. The number of participants, as well as means (standard deviations, SDs), median or % (numbers of patients), will be tabulated where appropriate.

**Table 2 Tab2:** Baseline characteristics for intervention and control group

	Intervention group (P4HP)	Control group (standard birth care)	Difference in means (95% CI)	*P*-value
	**Mean (SD)**	**Mean (SD**		
*Age*				
	**% (n)**	**% (n)**		
*Ethnicity (% native Dutch)*				
*Education (low, medium, high)*				
*Living situation (alone, with a partner, with children, with partner and children)*				
	**Mean (SD)**	**Mean (SD)**		
*BMI* *Diet quality (DHD2015-index)*				
*Empowerment (PRES)*				
*Sense of Coherence (SOC-3)*				
*Quality of Life (QoL VAS)*				
*Self-Rated Health (GSRH)*

**Table 3 Tab3:** Baseline, post-intervention, and change scores for intervention and control group

	T0 *(M, SD)*	T1 *(M, SD)*	Change T1 *(change ± SE)*	Effect estimate *(95% CI)*	Group differences *(P-value)*
BMI *(kg/m2)* Intervention (n=) Control (n=) Effect size					
Diet quality *(DHD2015-index)* Intervention (n=) Control (n=) Effect size					
Empowerment *(PRES)* Intervention (n=) Control (n=) Effect size					
Sense of Coherence *(SOC-3)* Intervention (n=) Control (n=) Effect size					
Quality of Life *(QoL VAS)* Intervention (n=) Control (n=) Effect size					
Self-Rated Health *(GSRH)* Intervention (n=) Control (n=) Effect size					

Linear mixed models will be used to analyse the data. Using linear mixed models allows for the analysis of different sources of variation in data and for unequal variances and correlations. This flexible method is suitable for analysis of the clustered data as it allows to calculate the treatment effect. When there are multiple levels, such as pregnant women seen by the same midwifery practice, the variability in the outcome can be thought of as either within-group or between-group. Pregnant women-level observations are not independent, as within a midwifery practice pregnant women and their guidance are more similar. Units samples at the highest level (in our research, midwifery practices) are regarded as independent. With this method also confounders can be taken into account [102]. After performing the linear mixed models analysis, the final results will be presented in Table 3. This table will display means and standard errors, the between-group differences, and the *p*-values for the treatment effect for all primary and secondary outcomes.

All primary and secondary outcomes will be tested via linear mixed models. Other subgroup analyses include age, ethnicity, individual or group (CenteringPregnancy) consultation, educational level, living situation, working situation, and income level. These variables will be checked if they differ across the groups using an independent Student’s t-test when continuous and normally distributed. If skewed, a Wilcoxon signed-rank test will be done. Variables that are not continuous, will be checked for differences between groups using a chi-square test. Two-sided *p* values < 0.05 will be regarded as statistically significant.

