### Sample size estimation

The sample size estimation is based on the design of a C-RCT [68] using the Group-or Cluster-Randomized Trials sample size calculator from the National Institutes of Health [69], where each cluster represents a midwifery practice. The results indicate that to detect an effect size of 0.4 (small to medium) [70] with a power of 80%, an alpha of 0.05, and an intra-cluster correlation coefficient of 0.02, each arm should include 7 clusters of 25 participants each. The assumption of an intra-cluster correlation coefficient of 0.02 is based on our experience with the SLIMMER project, a cluster randomized trial of a combined lifestyle intervention including behaviour change in diet and physical activity on overweight and risk of diabetes [71]. We strive to keep the number of participating pregnant women per cluster as similar as possible. Based on the sensitivity analysis for this sample size estimation [69], we estimate that 25 participants from 7 intervention and 7 control clusters – leading to 350 participants in total – will be sufficient to detect the relevant difference between groups. The Netherlands had 168.066 births in the year 2020 [72]. Three hundred fifty participants represent < 0.25% of pregnancies in the Netherlands, and therefore expected to be achievable.

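### Covariates are to be found by baseline tests between arms that ignore practice clustering: the tests are invalid here and are a poor way to choose what to adjust for

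*Protocol article*

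**What the plan says.** In the protocol article, Quantitative analyses C-RCT, chi-square tests for categorical variables and Student's t-tests for continuous ones "will be used to compare the descriptive statistics between study groups and to identify potential covariates". Table 2 lists ten baseline variables (age, ethnicity, education, living situation, BMI, diet quality, PRES, SOC-3, QoL and GSRH), with columns for the difference in means with 95% CI and for the p-value. The section ends with the general threshold, two-sided p "values < 0.05 will be regarded as statistically significant".

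The same section explains why outcomes go into linear mixed models: "Pregnant women-level observations are not independent, as within a midwifery practice pregnant women and their guidance are more similar". It adds that such models can take confounders into account, but gives no basis for choosing them other than the baseline tests. No allowance for clustering is stated for those tests.

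Under Cluster and participant recruitment, practices are randomised as clusters. Under Sample size estimation, the calculation uses "an alpha of 0.05, and an intra-cluster correlation coefficient of 0.02", with 7 clusters of 25 women per arm.

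**The concern.** Two separate faults sit in one sentence.

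- **The tests do not fit the design.** A t-test or chi-square test on individual women assumes independent observations. The section denies that assumption when it justifies the mixed models, and the sample size allows for its failure. Clustering is respected in the outcome model and ignored in the step that feeds it.
- **The tests answer the wrong question.** A between-arm p-value says how far a variable differs between arms. It does not say whether the variable predicts the outcome. Choosing on it can admit variables that do not matter and omit strong predictors that happen to be balanced.

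At stake are the p-values and intervals printed in Table 2, the choice of adjusted model for each outcome, and the precision of the treatment effect in a trial sized for 80% power with little to spare.

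**Working it through.** **Inputs.** From Sample size estimation: effect size 0.4 SD, power 80%, alpha 0.05, ICC 0.02, 7 practices per arm, 25 women per practice (175 per arm, 350 in total). From Table 2: ten variables. The article gives no ICC for any baseline variable. The value 0.02 is borrowed from the sample size, and all other ICCs below are assumptions.

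**The plan's own figure first.** Without clustering, an effect of 0.4 SD needs 2 × (1.96 + 0.84)² / 0.4², or 99 women per arm. The design effect is 1 + (25 − 1) × 0.02 = 1.48, giving 99 × 1.48 = 146.5 women, or 5.86 practices per arm on the normal approximation. With t quantiles on 2 × (7 − 1) = 12 degrees of freedom the need is 6.89, so 7 practices. Power is 80.6% with 7 and 72.8% with 6. The stated size is reproduced, so clustering was counted there.

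**False rejections of an unclustered baseline test.** With no true imbalance, the rate at nominal 5% is 2 × (1 − Φ(1.96 / √DE)), where DE = 1 + 24 × ICC. At ICC 0.02, 1.96 / √1.48 = 1.611, and the rate is 0.107. A simulation of 100,000 trials (7 against 7 practices of 25) gave 10.8%.

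| ICC of the baseline variable | Design effect | False rejection per test | At least one of 10 | Expected flags |
|---|---|---|---|---|
| 0 (a correct 5% test) | 1.00 | 5.0% | 40% | 0.5 |
| 0.01 (assumed) | 1.24 | 7.8% | 56% | 0.8 |
| 0.02 (plan's value) | 1.48 | 10.7% | 68% | 1.1 |
| 0.05 (assumed) | 2.20 | 18.6% | 87% | 1.9 |
| 0.10 (assumed) | 3.40 | 28.8% | 97% | 2.9 |

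The fourth column is 1 − (1 − rate)^10, for example 1 − 0.893^10 = 0.68, and assumes ten independent variables with the same ICC. If the interval in Table 2 comes from the same t-test, its coverage at ICC 0.02 is 100% − 10.7% = 89.3%, not 95%.

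**Does this reach the treatment effect?** The rule was simulated under no treatment effect: 14 practices of 25, ten covariates with ICC 0.02, screening at 0.05, then a generalised least squares test of treatment with the outcome ICC held at 0.02 and 12 degrees of freedom. Using the t critical value 2.179 with a known ICC makes this reference test conservative: 2 × (1 − Φ(2.179)) is about 2.9%.

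| Outcome variance explained by the covariates (assumed) | Type I error, unadjusted | Type I error, after screening |
|---|---|---|
| 30% | 2.7% | 2.1% |
| 50% | 3.0% | 1.3% |

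Screening lowered the error rate. A separate run gave the same picture: 2.5% and 1.7% after screening, against 3.0% unadjusted in both cases.

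**Precision.** With outcome variance 1, the unadjusted standard error is √(2 × 1.48 / 175) = 0.130. Adjusting in every trial for covariates that explain 50% gives 0.130 × √0.5 = 0.092. The simulated standard deviation after screening was 0.112. The variance ratio is (0.112 / 0.092)² = 1.48, so screening leaves about 48% more variance than a fixed prognostic set would.

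**The case against.** The best defence is that none of the false-flag rates concerns the trial's result. The outcomes are analysed with mixed models that recognise the practice level, and the simulations show no rise in false positives. This stands. A reader might infer that faulty screening inflates the type I error of the treatment effect; neither the plan's model nor the calculation supports that. The cost is a conservative error rate and lost precision.

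A reader might also infer that any flagged difference is chance, so that Table 2 would signal failed randomisation where there is none. The article does not support that either. Midwives cannot be blinded, and they recruit women purposively in practices already randomised, so real recruitment imbalance is possible. But an unclustered p-value cannot separate such imbalance from chance.

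Third, the article speaks only of potential covariates and does not say that p < 0.05 alone decides entry; a final list may sit in an analysis plan. That is fair, so it cannot be said that balanced predictors will be excluded, only that the stated method gives no reason to include them. The point is not a missing list. It is that the article fixes a method for finding covariates, and the method is unsound.

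Three smaller limits also stand:

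- The screening uses T0 data, not T1 outcomes, so it is not selection on the treatment effect.
- T0 outcome values may enter the analysis anyway, since T0 and T1 data are both used and Table 3 reports change, but the article does not say how.
- The later sentence beginning "These variables will be checked if they differ across the groups using an independent" follows the list of subgroup variables. It shows the same kind of test in use but is not evidence about covariate choice.

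**Conclusion.** Wrong as written, and it should be fixed. The baseline tests contradict the article's own account of the data. At its ICC of 0.02 they reject about 10.7% of the time instead of 5%, with about a 68% chance of at least one flag in ten variables against 40% for correct tests. Correlation among the variables would change the ten-variable figures, and ICCs other than 0.02 would change all of them.

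Correcting the tests for clustering would make Table 2 valid but would not rescue covariate selection, because imbalance is not prognostic value. The 48% excess variance assumes that every flagged variable, and no other, enters the model, and that the covariates explain half the outcome variance. The loss shrinks as that share falls.

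**What to change.** 1. In the sentence that introduces the chi-square and t-tests, strike the identification of covariates as a purpose.
2. In Table 2, remove the unclustered p-value and confidence interval. Describe each variable by arm, which keeps any recruitment imbalance visible. If a difference and interval are shown, compute them with allowance for practice.
3. Name the covariates before T1 data are seen: the T0 value of each outcome, plus a short list of prognostic variables already collected, chosen by the investigators on subject-matter grounds. Use them whatever the baseline comparison shows.
4. Report the model without that short list as a sensitivity analysis.

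The cost is wording in the analysis section and two columns of one table. No new data are needed, but the covariate list carries weight only if it is fixed before T1 data are seen.

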## Discussion

This paper describes the study protocol for a mixed methods study consisting of a C-RCT with an intervention group and a control group and a process evaluation. The study protocol includes the evaluation of P4HP, an empowerment intervention to improve diet quality among pregnant women. To our knowledge, this is the first C-RCT that evaluates the effectiveness of an empowerment intervention to improve diet quality in The Netherlands. Research in this field is needed because there is limited evidence of effective empowerment interventions regarding diet quality during pregnancy. To ensure that P4HP fits into standard birth care, various stakeholders have been involved in all steps of the development process. Our study will provide important and unique information on how to empower pregnant women to achieve improved diet quality by midwives and dieticians. Having both a quantitative and qualitative evaluation of P4HP will create a comprehensive overview of both the impact of P4HP and how best to implement it more broadly in practice.

P4HP will be assessed on diet quality, empowerment, SOC, QoL, and SRH. Although these assessments were selected intentionally based on previous research, the intervention may still produce an effect that is not directly assessed by our quantitative assessments. The process evaluation is therefore added to capture these indirect effects using semi-structured interviews. Innovative is that outcome measures include empowerment and SOC, something not common in C-RCT studies. Previous studies found evidence that SOC significantly changed and that those with a weaker SOC were more likely to have a stronger SOC after the intervention that included experimental learning [86, 104], as these groups have most to gain. In case we find change in SOC, it indicates that participants of P4HP benefit from the intervention; providing a more complete picture of the interventions’ successes. Two limiting factors of using Eetscore to assess diet quality are that it is only available in Dutch and oriented to a Dutch dietary pattern. Consequently, this unfortunately limits women who do not speak Dutch and with other diet patterns from participating.

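### The T0 score of each outcome is not a standing covariate: baseline tests are to identify covariates, and Table 3 is laid out around change without fixing the modelled outcome

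*Protocol article*

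**What the plan says.** All references are to the protocol article.

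- **Model.** Under Quantitative analyses C-RCT, every primary and secondary outcome is tested by a linear mixed model that allows for clustering by practice. If data are missing at random, "all available data from T0 and T1 will be used to conduct the analyses". The text does not say whether the modelled outcome is the T1 score, the change, or both time points. It lists no fixed effects.
- **Covariates.** The same section uses t-tests and chi-square tests between the arms at baseline to find possible covariates. Table 2 carries P-values for the T0 scores of all outcomes. The only other remark is that the method permits confounders to be included.
- **Results table.** Table 3 is titled "Baseline, post-intervention, and change scores for intervention and control group". Its columns are T0, T1, change with its SE, effect estimate with 95% CI, and a P-value for the group difference.
- **Planned size.** Sample size estimation sets 7 practices of 25 women per arm "to detect an effect size of 0.4 (small to medium"), without saying whether 0.4 is in SDs of the T1 score or of the change.
- **SOC.** The Discussion states: "In case we find change in SOC, it indicates that participants of P4HP benefit from the intervention".

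**The concern.** A baseline significance test is the wrong criterion for adjusting for T0. Any baseline difference between randomised arms is a chance one, and what makes T0 useful is its correlation with T1. A rule driven by baseline P-values can leave out a strongly prognostic T0 score because the arms happened to look alike. It also makes the model depend on the data.

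The Table 3 layout adds to this. Change is the only column headed with an SE, and it stands directly before the effect estimate. An analyst following the table could well report the difference between two mean changes. That estimate is never more precise than the T0-adjusted one and, at low r, is less precise than the T1 comparison alone. The sample size only just reaches its target power, so the choice of model matters.

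The SOC sentence names neither a comparator nor a direction, although the SOC section says that higher SOC-3 scores mean weaker SOC. It follows a remark that women with weaker SOC tended to gain most in earlier studies, a pattern that regression to the mean can also produce.

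**Working it through.** **Inputs from the article.** "an alpha of 0.05"; two-sided ("Two-sided *p* values < 0.05 will be regarded as statistically significant"); "with a power of 80" per cent; "an intra-cluster correlation coefficient of 0.02"; effect size 0.4; 7 practices of 25 women per arm (175 per arm, 350 in total).

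**Assumptions not in the article.** r is the T0–T1 correlation, shown from 0.2 to 0.8. The effect of 0.4 is in SDs of the T1 score. T0 and T1 have equal variance. The intra-cluster correlation is 0.02 for the T1, change and adjusted scores alike.

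**Step 1: reproduce the plan.**
- Design effect = 1 + (25 − 1) × 0.02 = 1.48.
- SE of the T1 difference = √(2 × 1.48 / 175) = 0.130 SD.
- Non-centrality = 0.4 / 0.130 = 3.08; degrees of freedom = 2 × (7 − 1) = 12.
- Power from the non-central t = 80.6%. With 6 practices per arm it is 72.8%, so 7 is the smallest number that reaches 80%.

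The stated size is reproduced.

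**Step 2: compare the two estimators.** Relative to the T1 difference, the variance is multiplied by 2(1 − r) for a difference in change and by 1 − r² for a T0-adjusted difference. The ratio of change to adjusted is 2(1 − r) / [(1 − r)(1 + r)] = 2/(1 + r). This is at least 1 for every r.

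**Step 3: put the numbers in.** Each SE is 0.130 times the square root of the factor.

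| r | Change: factor, SE | Power | T0-adjusted: factor, SE | Power | Variance ratio |
|---|---|---|---|---|---|
| 0.2 | 1.60, 0.165 | 60.8% | 0.96, 0.127 | 82.1% | 1.67 |
| 0.3 | 1.40, 0.154 | 66.6% | 0.91, 0.124 | 84.1% | 1.54 |
| 0.4 | 1.20, 0.142 | 73.2% | 0.84, 0.119 | 86.8% | 1.43 |
| 0.5 | 1.00, 0.130 | 80.6% | 0.75, 0.113 | 90.2% | 1.33 |
| 0.6 | 0.80, 0.116 | 88.4% | 0.64, 0.104 | 94.1% | 1.25 |
| 0.7 | 0.60, 0.101 | 95.3% | 0.51, 0.093 | 97.6% | 1.18 |
| 0.8 | 0.40, 0.082 | 99.4% | 0.36, 0.078 | 99.7% | 1.11 |

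Practices per arm needed for 80% power, change against adjusted: 10 against 7 at r = 0.3, 9 against 7 at r = 0.4, 7 against 6 at r = 0.5, and 6 against 5 at r = 0.6.

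**Step 4: chance imbalance.** If the T0 scores share the intra-cluster correlation of 0.02, the T0 difference between arms also has an SE of 0.130 SD. An imbalance of up to 2 × 0.130 = 0.26 SD is then ordinary. Given an observed imbalance D, the difference in change is off by (1 − r) × D. At r = 0.5 that is 0.5 × 0.26 = 0.13 SD, about a third of the target 0.4. Averaged over randomisations it cancels.

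**The case against.** The strongest reply is that the article does not commit the trial to change scores. A column of changes may be descriptive, and nothing says that the effect estimate is the difference between the two changes. A mixed model on T0 and T1 with a common T0 mean would fit the existing wording and be about as efficient as T0 adjustment. An article may also leave exact model terms to an analysis plan. All of this stands. A reader might infer from Table 3 that the effect is fixed as a difference in change; the text does not support that.

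Four other strong readings also fail.

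- *The trial is underpowered.* This needs r below 0.5 and 0.4 in SDs of the T1 score, and the article gives neither. If 0.4 is in SDs of the change, a change analysis has the planned 80.6%.
- *The T0 data are wasted.* A change score uses T0, only less efficiently.
- *Change scores are biased.* They are unbiased over randomisation, and off only conditionally on an observed imbalance.
- *SOC benefit could be claimed without a control comparison.* The Non-blinded C-RCT section evaluates outcomes between intervention and control practices, and the analysis section promises between-group tests for all of them. The Discussion sentence is loose wording and not an analysis rule.

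It can also be said that the baseline tests are only to suggest covariates, and are not declared the sole route into the model. That is fair. But it is the only route the article describes, and nothing exempts the T0 outcome scores listed in Table 2. Using baseline tests to choose covariates is stated in this document, so it can be faulted here.

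**Conclusion.** The point holds in a limited form. The plan gives the T0 score no standing place in the outcome models, describes a baseline-test route to covariates, and sets out its results around change while leaving the modelled outcome open. Fixed T0 adjustment improves on that at every r: it is never less precise than change, with a variance advantage of 2/(1 + r).

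The possible loss of power is conditional. If change were the estimand, 0.4 were in T1 SDs and the intra-cluster correlation were 0.02 on every scale, power would be 67% against 84% at r = 0.3 but 95% against 98% at r = 0.7. Below r = 0.5 change falls short of plan; at 0.5 it matches plan, and above that exceeds it. The SOC sentence needs rewording only. The correction should be made before analysis, but it does not call the design or the planned size into question.

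**What to change.** 1. For every outcome, state one model: a linear mixed model for the T1 score with arm and the woman's T0 score on that outcome as fixed effects, and practice as a random intercept. The mixed model on T0 and T1 with a common T0 mean in both arms is an acceptable alternative, and it also keeps women with only one time point.
2. State that the T0 score enters regardless of any baseline comparison, so that baseline P-values do not decide it.
3. In Table 3, define the effect estimate and its P-value as the T0-adjusted between-arm difference at T1, and label the change column descriptive.
4. Reword the Discussion sentence so that benefit on SOC is inferred from the between-arm difference at T1 adjusted for T0, with the direction given (a lower SOC-3 score means stronger SOC).
5. Say whether 0.4 is in SDs of the T1 score or of the change.

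The cost is wording only. T0 is already measured in both arms, and no extra women, practices or visits are needed.
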